#### Participant Screening and Recruitment

Screening of participants will be conducted by reviewing the patient registry at the identified PD clinic to identify potential participants. Medical records will then be used to assess eligibility, and those who do not meet the criteria, as shown in Textbox 1, will be excluded. Eligible participants will be contacted via phone to receive a brief explanation of the study, and those who have expressed interest in participating or provided verbal consent will be scheduled for a physical screening visit at the clinic. During the screening visit, the participants will be provided with the participant information sheet and informed consent form, available in both Malay and English languages. They will be given ample time to review the study details before providing written consent, and only participants who have signed the consent form will be assigned a screening ID.

Participant inclusion and exclusion criteria.
**Inclusion criteria**
Adult outpatients (aged >18 years) attending peritoneal dialysis (PD) clinic visitsHave undergone peritoneal dialysis for at least 6 monthsHave a serum albumin level <40 g/LHave a malnutrition inflammation score of mild, moderate, or severeAgreed to follow the dietary instructions based on the randomization assignmentAgreed to attend baseline visits and additional follow-up appointments at months 1, 3, and 6 postrandomization, either in person or via telehealth, and respond to monthly or more frequent phone calls
**Exclusion criteria**
Have been hospitalized for the past 3 monthsHave ongoing infection or sepsisHas undergone surgery in the past 6 monthsHave high inflammatory diseases, malignancy, or cancerHave dialysis adequacy of <1.2 kt/V

#### Participant Withdrawal and Dropouts

Throughout the 6-month study period, the participants will be monitored for adherence and motivation. The specific criteria for withdrawal and dropout are as follows: (1) missing ≥50% of follow-up visits during the 6-month study, (2) <50% compliance at 3 consecutive monthly review points based on the dietary compliance scoring system (scoring criteria are informed by clinical relevance, current dietary guidelines, and prior literature), (3) failure to comply with the study protocol, (4) voluntary withdrawal from the study, and (5) identification of a clinical condition requiring intervention or likely to affect study outcomes.

To manage dropouts, participants who withdraw, fail to meet compliance, or are lost to follow-up will be seen by an investigator. Reasons for failure to comply with the study protocol will be documented. Data collected up to the point of withdrawal will be retained and analyzed unless requested otherwise by the participant. Participants withdrawn from the study will not be replaced, as the sample size calculation includes an allowance for dropouts.

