#### Research Flow

This study protocol is adapted from a similar ongoing clinical trial involving patients with CKD with diabetes mellitus in the United States [16]. Figure 1 shows a diagram outlining the research flow. The study begins with participant screening, recruitment, and baseline assessment conducted on the same day. Following baseline assessment, participants are then randomized into either the intervention group receiving a plant-focused dietary intervention or the control group receiving a standard renal dietary intervention.

A 2-week familiarization phase is implemented immediately after randomization as part of the intervention period. During this phase, participants begin following their assigned dietary intervention and receive additional guidance and closer monitoring to support early adaptation and adherence. This phase is intended to facilitate understanding of the dietary protocol and to identify and address potential challenges early, rather than to assess eligibility or introduce selection bias.

Participants from both groups are instructed to continue the assigned dietary intervention for 6 months. Key outcome assessments are conducted at baseline (0 months), midpoint (3 months), and end line (6 months). Data collected will be analyzed for subsequent report writing and publication.

The intervention and study procedures, including screening, recruitment, data collection, and intervention delivery, will be conducted by a registered dietitian. Health care staff at the study site will assist with clinical procedures such as blood collection.

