#### Sample Size

The sample size was calculated using the standard formula for comparing 2 independent means in a parallel-group design using several assumptions.

On the basis of previous studies in dialysis populations, an estimated SD of 5 g/L was used to account for heterogeneity and to avoid underestimation of sample size. Notably, studies by Kalantar-Zadeh et al [17] and Rambod et al [18] reported serum albumin SDs ranging from 1.9 to 4.4 g/L, while a study by Limwannata et al [19] reported an SD of 5.0 g/L.

A clinically meaningful difference (δ) of 3 g/L (0.3 g/dL) was selected as it is consistent with differences in serum albumin levels observed across dialysis populations in previous studies. For instance, variations of 0.3 to 0.4 g/dL are observed between cohorts reported in studies by Rambod et al [18] and Limwannata et al [19]. Additionally, serum albumin is a well-established predictor of morbidity and mortality in patients undergoing dialysis, and even modest changes are considered clinically relevant in reflecting improvements in nutritional status [17].

Using the formula mentioned below, a 2-sided significance level of.05 (Zα/2=1.96) and 80% power (Zβ=0.84) were used to calculate the sample size. As a result, a minimum of 44 participants per group was required. After accounting for an anticipated 10% dropout rate, the sample size was rounded up to 50 participants for each group, with a total sample size of 100 participants. As repeated measurements will be conducted at baseline, 3 months, and 6 months, the calculated sample size is considered conservative.

The sample size was calculated using the standard formula for comparing 2 independent means in a parallel-group design, as shown below:

[figure not shown]

Where n is the sample size per group, Zα*/*2 is the standard normal deviate for a 2-sided significance level (1.96 for *α*=.05), Zβ is the standard normal deviate for power (0.84 for 80% power), σ is the SD, and δ is the expected difference between groups.

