#### Intervention Group vs Control Group

The control group will follow a standard renal diet and be encouraged to maintain their usual dietary and physical activity patterns, with guidance to ensure that at least 50% of their total protein intake comes from high biological value animal-based sources. The standard renal diet was chosen as comparator as it reflects the current clinical practice. In contrast, the intervention group will follow a plant-focused dietary pattern that emphasizes plant-based foods, such as fruits, vegetables, legumes, whole grains, nuts, seeds, and plant oils, with minimal reliance on animal-based products. Participants in the intervention group will be required to consume plant-focused meals for most of their daily meals. For example, those consuming 3 meals per day must ensure that at least 2 out of the 3 meals are plant based, while those consuming 4 meals per day must ensure that at least 3 out of the 4 meals are plant based. The remaining meal or snack may include either plant- or animal-based foods to support flexibility and adherence.

Participants in both groups will receive individualized dietary counseling at each data collection point (baseline, 3 months, and 6 months). In addition, participants are also provided with educational pamphlets and 14-day structured meal plans that incorporate natural food sources and culturally appropriate meal choices. Meal plans for both groups are developed in accordance with the Malaysian Medical Nutrition Therapy Guidelines for Chronic Kidney Disease and the Kidney Disease Outcomes Quality Initiative Clinical Practice Guidelines for Nutrition in CKD [7,21]. Throughout the study, participants will continue to receive standard medical care, with no specific concomitant care prohibited.

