### Data Collection Procedures

#### Overview

The parameters assessed at each participant visit, from screening through the 6-month study duration, are summarized in Table 1. Data will be collected through various questionnaires and standardized procedures. All questionnaires used are freely and publicly accessible.

**Table 1 table1:** Summary of parameters assessed during participant visits.

Variables			Screening		Month 0		Month 3		Month 6

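### The attendance criterion for withdrawal has no fixed denominator: missing only month 3 meets it on a two-visit schedule (months 3 and 6) but not on a three-visit schedule (months 1, 3 and 6)

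*Protocol article*

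**What the plan says.** The first criterion under Participant Withdrawal and Dropouts is "missing ≥50% of follow-up visits during the 6-month study". That section neither names nor numbers the visits, and it does not say when the criterion is assessed.

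Two schedules appear elsewhere in the protocol article:

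- **Three visits after baseline.** The inclusion criteria require agreement to "additional follow-up appointments at months 1, 3, and 6 postrandomization, either in person or via telehealth".
- **Two visits after baseline.** The Overview of the data collection procedures states: "The parameters assessed at each participant visit, from screening through the 6-month study duration, are summarized in Table 1". The columns of that table are Screening, Month 0, Month 3 and Month 6; there is no month 1. Two other sections give the same time points. Research Flow says "Key outcome assessments are conducted at baseline (0 months), midpoint (3 months), and end line (6 months"), and Intervention Group vs Control Group promises "individualized dietary counseling at each data collection point (baseline, 3 months, and 6 months").

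The withdrawal section also says that data gathered before withdrawal are kept and that withdrawn participants are not replaced. Statistical Analysis specifies intention to treat, with last observation carried forward for missing data.

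**The concern.** A percentage threshold is only a rule once its denominator is fixed. With so few visits, one visit more or less changes the outcome, and the inclusive sign matters because one of two is exactly 50%. The case that divides the two schedules is a simple one: a single missed visit.

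What is at stake is the primary outcome, the change in serum albumin from baseline to 6 months. If a participant absent only at month 3 is withdrawn at that point, the month 6 albumin is not collected although the participant might have attended. With no month 3 value either, the last observation is the baseline one, and carrying it forward records a change of zero. The trial is open-label, and a registered dietitian both delivers the intervention and collects the data, so a rule with two readings could be applied by someone who knows the arm.

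**Working it through.** **The plan's own figure.** The only computed figure in the article is the sample size. With SD 5 g/L, difference 3 g/L, two-sided alpha 0.05 (1.96) and 80% power (0.84):

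n per group = 2 × (1.96 + 0.84)² × 5² / 3² = 2 × 7.84 × 25 / 9 = 43.6, so 44. Allowing for 10% dropout: 44 / 0.9 = 48.9, so 49, which the plan rounds up to 50. The figure reproduces and is not in dispute.

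**The criterion on each schedule.** Share missed = visits missed / visits scheduled, compared with 0.50.

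| Visits missed | Months 3 and 6 | Months 1, 3 and 6 | Same answer? |
|---|---|---|---|
| 1 only | 0/2 = 0%, kept | 1/3 = 33.3%, kept | yes |
| 3 only | 1/2 = 50%, withdrawn | 1/3 = 33.3%, kept | **no** |
| 6 only | 1/2 = 50%, withdrawn | 1/3 = 33.3%, kept | **no** |
| 1 and 3 | 1/2 = 50%, withdrawn | 2/3 = 66.7%, withdrawn | yes |
| 1 and 6 | 1/2 = 50%, withdrawn | 2/3 = 66.7%, withdrawn | yes |
| 3 and 6 | 2/2 = 100%, withdrawn | 2/3 = 66.7%, withdrawn | yes |

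The schedules disagree in two cases. For a miss at month 6 only, the month 6 visit is missed on either count, so only the label changes. For a miss at month 3 only, a month 6 value that could have been obtained may be lost.

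**Illustration of size.** The article gives no missed-visit rate. Assume that each visit is missed independently with probability p. The share who miss month 3 but could attend month 6 is p(1 − p):

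- p = 5%: 0.05 × 0.95 = 4.8%, or about 2.4 of 50 per arm
- p = 10%: 0.10 × 0.90 = 9.0%, or 4.5 of 50
- p = 15%: 0.15 × 0.85 = 12.8%, or about 6.4 of 50

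These are the people whose month 6 value is at risk on the two-visit count. A fraction p of them would also have missed month 1 and would meet the criterion on either schedule. The share on whom the two schedules actually differ is therefore p(1 − p)²: 4.5%, 8.1% and 10.8%. If absences cluster within participants, the shares would be smaller for the same p.

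**The case against.** The strongest reply is that the text nearly supplies the denominator. The criterion speaks of follow-up visits, and only the inclusion criteria list follow-up appointments, at months 1, 3 and 6. Research Flow speaks of key outcome assessments, and the intervention section of data collection points. A month 1 contact without an outcome battery would fit all of these, and on that reading nobody is withdrawn for missing month 3 alone. This is plausible and may be what was intended. It does not settle the matter: Table 1 is introduced as covering each visit, it has no month 1, and nothing ties the withdrawal section to the inclusion criteria.

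A second reply is that removal at month 3 is inferred. The criterion counts misses over the 6 months and could be a classification made at the end. That stands, so the consequence for the primary outcome is conditional. On a two-visit count, however, 50% is already reached at month 3, and nothing tells staff to wait. Laboratory values are also to be taken from hospital records, so a routine albumin might exist despite a missed visit. The article does not say that records after withdrawal would be used.

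A reader might infer more than the article supports:

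- **A third denominator of six monthly contacts.** The monthly reviews belong to a separate criterion ("<50% compliance at 3 consecutive monthly review points based on the dietary compliance scoring system"), and the phone calls are listed apart from appointments. Neither is called a visit.
- **Dropout at about twice the allowance.** At p = 10% the two-visit count captures 1 − 0.9² = 19%, but 10 percentage points of that are people who miss month 6 itself, whose visit is lost on either count.
- **Power falling to about 75%.** That is a t test on about 40 observed month 6 values per arm. The planned analysis carries values forward in a repeated-measures model, so withdrawn participants stay in it. The harm is a substituted value, not a smaller n.
- **The rule deciding the retention rate.** Retention is an exploratory outcome, and no section defines it by this criterion.

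**Conclusion.** The inconsistency is in the current text and needs no assumption: the same attendance record meets the withdrawal criterion on one stated schedule (50%) and not on the other (33%). It is more than an omitted detail, because the article prints a numerical threshold alongside two incompatible visit lists.

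The effect on the primary outcome is conditional. It requires that the two-visit count is used, that it is applied when month 3 is missed, and that no later albumin is obtained by another route. Its size is unknown. The range of about 4.8% to 12.8% of participants rests on assumed miss probabilities of 5% to 15% and on independence between visits, and is only an illustration. The point should be corrected, but it does not undermine the sample size or the design.

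**What to change.** 1. Reconcile Research Flow, the inclusion criteria, Participant Withdrawal and Dropouts, Intervention Group vs Control Group, and Table 1 to one list of follow-up visits, stating whether month 1 is on it. Which schedule is right is for the sponsor.
2. State the attendance criterion as a count of missed visits on that list. The number is also the sponsor's choice.
3. State that meeting the criterion does not stop collection of the month 6 albumin from a participant who is willing to attend. This concerns outcome data only and leaves clinical management untouched.

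The cost is wording in a few sections and one table, with no new visits. The small downside is that a few poor attenders are followed to month 6. Only 9 of the planned 100 participants had been recruited when the article was submitted, so an early correction could precede most withdrawal decisions.

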### Research Objectives

The primary objective is to determine the effect of a plant-focused dietary intervention on changes in serum albumin from baseline to 6 months compared with standard-of-care renal diet in malnourished patients undergoing PD.

The secondary objectives are (1) to determine the effect of a plant-focused dietary intervention on changes in anthropometric measurements (BMI, TSF, and MAMC), biochemical and inflammatory markers (lipid profile, hs-CRP, and renal parameters), dietary adequacy and nutrient intake, MIS scores, physical function and muscle strength, QOL, appetite scores, and dialysis adequacy from baseline to 6 months compared with standard-of-care renal diet in malnourished patients undergoing PD and (2) to determine the baseline nutritional status of malnourished patients undergoing PD, including their knowledge, attitude, and practices of renal diet intake, as well as sociodemographic characteristics and medical history.

Exploratory objectives are to assess adherence to a plant-focused dietary intervention over the 6-month period and to evaluate retention rates over 6 months of intervention.

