### Statistical Analysis

Statistical methods are detailed in Table 4. Data will be analyzed using SPSS (version 28; IBM Corp). Normality of continuous data will be tested using the Kolmogorov-Smirnov test.

**Table 4 table4:** Summary of the statistical analysis.

Study outcomes	Variables	Statistical analysis
Primary or main outcome	Serum albumin	GLM^a^-repeated measures (time×group interaction)
Secondary outcomes	Anthropometric data Biochemical data Dietary adequacy Physical function Quality of life Appetite and food satisfaction Dialysis adequacy	GLM-repeated measures (time×group interaction)
Exploratory or feasibility outcomes	Dietary adherence or compliance Retention rate	Descriptive statistics and chi-square test

^a^GLM: generalized linear model.

The primary analysis will evaluate changes in serum albumin from baseline to 3 and 6 months between intervention and control groups. A generalized linear model for repeated measures will be used to assess time, group, and interaction effects. Analyses will follow the intention-to-treat principle, with missing data handled using the last observation carried forward method. Adjustment for potential confounders such as age, sex, dialysis duration, and baseline nutritional status will be performed using multivariable models. Bonferroni correction will be applied for multiple comparisons. Secondary outcomes, including anthropometric, biochemical, dietary, MIS, physical function, QOL, appetite, and dialysis adequacy parameters, will be analyzed using similar repeated-measures approaches. Statistical significance will be set at *P*<.05.

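### Withdrawal for missed visits can replace an obtainable month 6 albumin with a carried-forward value, and the rule does not name the visits it counts

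*Protocol article*

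**What the plan says.** Under Participant Withdrawal and Dropouts, the first criterion is "missing ≥50% of follow-up visits during the 6-month study". The same section adds: "Data collected up to the point of withdrawal will be retained and analyzed unless requested otherwise by the participant". Withdrawn participants are not replaced. Under Statistical Analysis: "Analyses will follow the intention-to-treat principle, with missing data handled using the last observation carried forward method". The primary objective is the change in serum albumin from baseline to 6 months.

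Two other statements bear on whether the month 6 value could be had anyway. Biochemical Data takes laboratory parameters from hospital records. Overall Study Design and Intervention Group vs Control Group say that the study runs alongside routine PD clinic visits and that standard medical care continues.

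On which visits count, the inclusion criteria in Textbox 1 have participants agree to "follow-up appointments at months 1, 3, and 6 postrandomization, either in person or via telehealth, and respond to monthly or more frequent phone calls". Table 1 is introduced with "The parameters assessed at each participant visit, from screening through the 6-month study duration, are summarized in Table 1", and its only columns after baseline are months 3 and 6. Research Flow and Intervention Group vs Control Group also give baseline, 3 and 6 months, as the points for assessment and counselling.

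An exploratory objective is "to evaluate retention rates over 6 months of intervention".

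**The concern.** Intention-to-treat asks for the month 6 outcome of everyone randomised, whether or not they attended. Criterion 1 turns poor attendance, which arises after randomisation, into a ground for ending participation. The only statement about such participants' data stops at withdrawal, and carry-forward then fills the gap. If baseline is the last value, the participant enters the primary analysis with a change of zero that nobody observed.

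The gap in that case need not come from the participant. A missed study visit does not mean that no albumin was measured, since the laboratory values come from routine records. If attendance differed between the two diets, the carried-forward values would also be spread unevenly over the arms.

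The unnamed denominator adds to this. The limit is set at 50% or more, so the number of visits counted decides whether one missed visit can trigger the rule. Retention depends on the same count.

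**Working it through.** **1. The plan's own figure.** Inputs from Sample Size: SD 5 g/L, difference 3 g/L, z values 1.96 and 0.84, dropout 10%.

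n = 2 × 5² × (1.96 + 0.84)² / 3² = 2 × 25 × 7.84 / 9 = 43.56, so 44 per group. 44 / 0.90 = 48.9, so 49, rounded up to 50. The figure is reproduced and is not in dispute. The allowance ("After accounting for an anticipated 10% dropout rate, the sample size was rounded up to 50 participants for each group") covers lost numbers. It does not cover the effect of a substituted outcome value.

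**2. When criterion 1 is met.** Missed visits divided by counted visits, against a limit of 50% or more:

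| Visits missed | Counting months 1, 3, 6 | Counting months 3, 6 |
|---|---|---|
| 1 only | 1/3 = 33%, stays | 0/2 = 0%, stays |
| 3 only | 1/3 = 33%, stays | 1/2 = 50%, withdrawn |
| 6 only | 1/3 = 33%, stays | 1/2 = 50%, withdrawn |
| 1 and 3 | 2/3 = 67%, withdrawn | 1/2 = 50%, withdrawn |
| 1 and 6 | 2/3 = 67%, withdrawn | 1/2 = 50%, withdrawn |
| 3 and 6 | 2/3 = 67%, withdrawn | 2/2 = 100%, withdrawn |

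**3. What follows for month 6 albumin.** On either count the limit can be reached before month 6: by missing months 1 and 3 on the three-visit count, or month 3 alone on the two-visit count.

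- If the rule is acted on then, and collection stops, month 6 is missing and is carried forward. With no month 3 value either, the recorded change is baseline minus baseline = 0.
- If month 6 itself is the missed visit, the month 3 value is carried forward, unless a routine result near month 6 is used.
- If the rule is judged only after month 6, an attended month 6 value is kept, but the participant may still be counted as a dropout.

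**4. Illustration of size.** Let p be the probability of missing a visit, independent between visits. Neither p nor independence is in the article. Withdrawn by criterion 1: 3p²(1−p) + p³ for three visits, 1 − (1−p)² for two. Participants withdrawn before month 6 who would have attended it: p²(1−p) for three visits, p(1−p) for two. Per 100 participants:

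| p | Withdrawn, three visits | Withdrawn, two visits | Month 6 attender lost, three visits | Month 6 attender lost, two visits |
|---|---|---|---|---|
| 2% | 0.1 | 4.0 | 0.04 | 2.0 |
| 5% | 0.7 | 9.8 | 0.2 | 4.8 |
| 10% | 2.8 | 19.0 | 0.9 | 9.0 |

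Criterion 1 alone would use up the 10% dropout allowance at p = 19.6% on three visits (3 × 0.196² − 2 × 0.196³ ≈ 0.10) and at p = 5.1% on two (1 − √0.90 = 0.051).

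Missed visits often cluster in the same people. At the extreme, where a person misses all visits or none, both counts withdraw a proportion p. Independence therefore tends to understate the three-visit figure and overstate the two-visit figure. Participants who cluster in this way also miss the month 6 visit, so hospital records are then the only source of a month 6 albumin.

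**The case against.** A reader might infer that the article sets two rival follow-up schedules, so that someone who misses only month 3 is withdrawn under one and kept under the other. The text does not support that. Textbox 1 is the only place that attaches months to follow-up appointments, and criterion 1 speaks of follow-up in the same way. Table 1 summarises parameters measured, and the other sections describe assessment or data collection points. Nor is Table 1 a list of every contact: food diaries are kept monthly, yet after baseline it shows food records only at months 3 and 6. Three visits is the natural count. What stands is a wording gap, because the rule names no visits and Table 1 is introduced as covering every participant visit.

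The harm to the primary outcome also needs several steps that the article does not state: the rule is acted on before month 6, withdrawal ends collection, and no routine result is used. Nothing expressly bars later collection. This stands as a limit on certainty, and the harm is therefore a possibility that the wording leaves open. But the article closes off none of these steps, and it names carry-forward as the answer to missing data.

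A reader might also infer that the rule would be applied differently in the two arms because the trial is open-label. The same text governs both arms, and nothing suggests two denominators.

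Finally, an article condenses a protocol, and the definition of a visit may be set out elsewhere. That excuses much of the denominator point. It does not remove the combination of withdrawal rule, data statement and carry-forward, all of which are printed here.

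**Conclusion.** The point holds in this form: as written, withdrawal for missed visits can put an earlier albumin in place of a month 6 value that hospital records could supply, in an analysis described as intention-to-treat. This is so on either count of visits. The unnamed denominator is a secondary wording matter, though it determines whether one missed visit is enough.

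The size is unknown. On the natural three-visit count, with independent misses at 5% to 10%, few month 6 attenders would lose their value (0.2 to 0.9 of 100). On the two-visit count it would be 4.8 to 9.0. These are illustrations only, since they rest on an assumed p and on independence. The conclusion further assumes that the rule is acted on when it is met, that withdrawal ends collection (implied but not stated), and that serum albumin is among the laboratory parameters taken from hospital records. The sample size is unaffected. The change is worth making because it protects the primary outcome at very little cost.

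**What to change.** Add to the withdrawal section that meeting criterion 1 ends study counselling but not outcome collection, and that month 6 albumin is still taken from hospital records where a routine result exists, unless the participant withdraws consent. In criterion 1, name months 1, 3 and 6 as the visits that count, in person or by telehealth. Show month 1 in Table 1 as a contact without outcome measures.

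The cost is one or two sentences, one table column and an ethics notification, with no new visit or blood sample. There are three downsides. Participants who have left the diet remain in the month 6 comparison, as intention-to-treat already implies. Some may have no routine albumin near month 6. A missed month 3 value would still be carried forward, which this change does not address.

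Recruitment began in March 2026 and 9 participants had been recruited at submission, so the change is best made before the first of them reach month 3.

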#### Biochemical Data

Laboratory parameters (renal, lipid, glucose, inflammation, dialysis adequacy, and protein intake) will be extracted from hospital records. hs-CRP will be analyzed externally using 10 mL fasting blood samples collected by trained staff.

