#### Dietary Assessment and Compliance Toward Diet Regime

Participants will complete a 3-day food diary monthly (2 weekdays and 1 weekend). At the first clinic visit, participants will receive training on how to accurately record only foods and beverages consumed using household measurements and a colored food album to assist with portion size estimation. Dietary intake data will then be analyzed using Nutritionist Pro (version 5.1.0; Axxya Systems [22]) using information from the Nutrient Composition of Malaysian Foods and Singapore Food Composition Book (Ministry of Health Singapore [23,24]).

Dietary adherence will be evaluated using a binary compliance scoring system, as detailed in Tables 2 and 3. Although arbitrarily set, the scoring categories were informed by clinical relevance, current dietary guidelines (medical nutrition therapy and Kidney Disease Outcomes Quality Initiative), and prior literature on compliance assessment in chronic disease populations [7,21,25].

**Table 2 table2:** Dietary compliance scoring system (scored per day).

Category				Scoring criteria^a^		
				Score=0		Score=1

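### Withdrawing participants from the study for poor adherence or clinical events means month-6 albumin is observed only in those not withdrawn and carried forward for the rest

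*Protocol article*

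**What the plan says.** Participant Withdrawal and Dropouts lists five criteria, and each takes the participant out of the study. The first is absence from at least half of the follow-up visits, and the fourth is the participant's own choice. The other three read "2) <50% compliance at 3 consecutive monthly review points based on the dietary compliance scoring system", "3) failure to comply with the study protocol" and "5) identification of a clinical condition requiring intervention or likely to affect study outcomes". On data, the section says: "Data collected up to the point of withdrawal will be retained and analyzed unless requested otherwise by the participant". It adds that withdrawn participants are not replaced because the sample size already allows for dropout. It says nothing about measuring outcomes after withdrawal.

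Statistical Analysis says: "Analyses will follow the intention-to-treat principle". Missing values are filled by LOCF. The primary objective is the change in serum albumin from baseline to 6 months.

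On the arms, Intervention Group vs Control Group asks controls to keep their habitual eating and activity, with guidance on animal protein. The intervention arm must make at least two of three, or three of four, daily meals plant based. The trial is unblinded, and under Research Flow a registered dietitian both delivers the intervention and collects data.

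**The concern.** Poor adherence and intercurrent clinical conditions arise after randomisation and may be related both to the assigned diet and to albumin. Under these rules they decide who has a measured month-6 value. The criterion on "identification of a clinical condition requiring intervention or likely to affect study outcomes" selects on expected outcome directly, and the criterion on protocol non-compliance has no threshold. Both are applied by staff who know the allocation.

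The arms ask for different amounts of change, so withdrawal could be unequal. The 6-month contrast would then compare a mixture of measured values and earlier carried-forward values, with different proportions in each arm. An albumin fall that continued after withdrawal would not be seen. Retention, which is an exploratory outcome, would also be produced in part by the study's own withdrawal rule.

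**Working it through.** **The plan's own figure.** Inputs from Sample Size: SD 5 g/L, difference 3 g/L, two-sided 5%, 80% power. n = 2 × (5 × (1.96 + 0.84) / 3)² = 43.56, so 44 per group. 44 / 0.90 = 48.9, so 49, which the document rounds up to 50. The stated figures reproduce. Withdrawals under the criteria draw on this same 10% allowance. Power for 3 g/L is 85.1% with 50 observed month-6 values per arm, 81.2% with 45, 76.5% with 40 and 70.9% with 35.

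**Bias formula.** Let pI and pC be the proportions withdrawn in the intervention and control arms. Let d be the mean albumin change between the last recorded value and month 6 among those withdrawn, taken as equal in both arms. LOCF omits p × d from each arm mean, so:

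plan's difference − full-follow-up difference = −(pI − pC) × d

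The document gives neither p by arm nor d. The values below are assumptions:

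- Equal withdrawal: 0.
- 20% vs 10%, d = −4 g/L: 0.10 × 4 = 0.4 g/L, which is 13% of the 3 g/L target.
- 30% vs 10%, d = −6 g/L: 0.20 × 6 = 1.2 g/L, which is 40% of the target.

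In the last two cases the plan flatters the intervention arm. If controls were withdrawn more often, the sign would reverse. If d differed between arms, equal withdrawal would not guarantee zero bias.

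For scale, the standard error of a difference in means with SD 5 and 50 per arm is 5 × √(2/50) = 1.0 g/L.

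**Effect on type I error.** A simulation took a true 6-month difference of 0 (4000 runs, 50 per arm, SD 5, correlation 0.6 between months 3 and 6, t test at month 6 in place of the planned model). Withdrawn participants were set D g/L below their arm mean at month 6, with half or none of that gap already visible in the carried-forward value.

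| Withdrawn | D (g/L) | Gap visible | LOCF difference (g/L) | Rejection rate |
|---|---|---|---|---|
| 10% vs 10% | 3 | half | −0.03 | 5.6% |
| 20% vs 10% | 3 | half | 0.15 | 4.8% |
| 30% vs 10% | 3 | half | 0.30 | 5.9% |
| 30% vs 10% | 5 | half | 0.48 | 7.6% |
| 30% vs 10% | 3 | none | 0.59 | 8.4% |
| 30% vs 10% | 5 | none | 1.01 | 16.9% |

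These agree with the formula, for example 0.20 × 0.5 × 3 = 0.3 and 0.20 × 5 = 1.0. With full follow-up the estimate stayed within 0.03 of zero and rejection was between 4.8% and 5.7%.

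**Timing.** The compliance criterion needs three consecutive monthly reviews and cannot act before the third, so a month-3 albumin will usually exist to carry forward. The protocol-failure and clinical-condition criteria can act earlier and may leave only baseline.

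**The case against.** The strongest reply is that nobody is dropped. Data from withdrawn participants are kept and analysed, and LOCF gives each a month-6 value in the randomised arm. A reader might infer that the plan excludes non-adherers and so contradicts its intention-to-treat statement outright. The text does not support that. The weaker point stands: the analysis set is preserved, but month-6 outcomes are observed selectively.

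A reader might also infer that the compliance score itself is stacked against the intervention arm. Only 1 of the 7 daily points in Table 2 is arm-specific. A participant who fails it every day but meets the rest scores 18/21 (86%), well above the 50% cut in Table 3. Failing the assigned protein source alone cannot trigger withdrawal under this criterion. That the plant-focused diet is harder to follow is inferred from the arm descriptions and is not stated.

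A third tempting reading is that the visit and diary schedules conflict, so that missing month 3 alone would be 50% of visits. Textbox 1 lists follow-up at months 1, 3 and 6, so missing month 3 is one of three. Table 1 summarises parameters assessed at visits, and Research Flow speaks of key assessments at 0, 3 and 6 months. A month-1 contact without a measurement battery fits both. The diary instruction, "Participants will complete a 3-day food diary monthly (2 weekdays and 1 weekend", fits the monthly calls. No contradiction is shown.

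Finally, a condensed article may leave post-withdrawal follow-up to a fuller protocol. That is fair as far as silence goes. However, the article writes the criteria as leaving the study and charges those losses to the dropout allowance, which implies that no month-6 value is expected.

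**Conclusion.** The concern holds in this form: as written, observed month-6 albumin comes only from participants not withdrawn for adherence or clinical reasons, and LOCF supplies the rest under an intention-to-treat label. Unequal withdrawal would bias the primary contrast.

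Direction and size cannot be derived from the document. The 0.4 and 1.2 g/L figures restate assumed withdrawal rates and hidden changes. The larger one needs three times the planned dropout in one arm and a hidden fall of twice the target difference. At 0.4 g/L the bias is less than half a standard error. The figures show what the rule could do and do not forecast what it will do. This is a point that should be fixed, not one that invalidates the design.

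**What to change.** In Participant Withdrawal and Dropouts, separate discontinuing the assigned diet from leaving the study, without changing any clinical rule on when the diet stops. State that participants who meet criteria 1, 2, 3 or 5 remain in follow-up, and that their month-3 and month-6 albumin are collected and analysed in the randomised arm unless consent is withdrawn. Report diet discontinuation separately from study retention.

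Biochemical Data says laboratory parameters "will be extracted from hospital records". Albumin is not named in that list, and nothing says that routine values will exist at months 3 and 6 for withdrawn participants. The team should confirm this. Where no routine value exists, a study sample would be needed.

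The cost is a wording amendment and slight extra data collection, with 9 participants recruited at submission. The downside is that the estimate will include non-adherers and may be smaller.
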